## Abstract

**Introduction:**

Gestational diabetes mellitus (GDM) is a state of glucose intolerance with onset during pregnancy. GDM carries prenatal and perinatal risks as well as long-term risks for the mother and her child. GDM may be involved in the foetal programming of long-term cardiovascular health. However, evidence is sparse and the effect of GDM on cardiovascular health is unknown. To address these issues, we will conduct MySweetHeart Cohort study. The objectives are to assess the effect of GDM on offspring’s cardiovascular health early in life by using surrogate markers of cardiovascular disease and atherosclerosis.

**Methods and analysis:**

This is a cohort study of 100 offspring of women with GDM and 100 offspring of women without GDM. At inclusion, a baseline assessment of the mothers will be conducted through means of self-report questionnaires, a researcher-administrated interview, blood pressure and anthropometric measurements, and a maternal blood sampling. Between the 30th and 34th weeks of gestation, a foetal echography will be performed to assess the foetal cardiac structure and function, the fetomaternal circulation and the hepatic volume. At birth, maternal and neonatal characteristics will be assessed. An echocardiography will be performed to assess cardiac structure and function 2–7 days after birth; carotid intima-media thickness will be also measured to assess vascular structure. MySweetHeart Cohort is linked to MySweetHeart Trial (clinicaltrials.gov/ct2/show/NCT02890693), a randomised controlled trial assessing the effect of a multidimensional interdisciplinary lifestyle and psychosocial intervention to improve the cardiometabolic and mental health of women with GDM and their offspring. A long-term follow-up of children is planned.

**Ethics and dissemination:**

Ethical approval has been obtained through the state Human Research Ethics Committee of the Canton de Vaud (study number 2016–00745). We aim to disseminate the findings through regional, national and international conferences and through peer-reviewed journals.

**Trial registration number:**

ClinicalTrials.gov (clinicaltrials.gov/ct2/show/NCT02872974).

Strengths and limitations of this studyThis study will increase our understanding of the impact of gestational diabetes mellitus on cardiometabolic health during foetal and neonatal periods. Within a Developmental Origin of Health and Disease framework, it will contribute to improving the knowledge on the early life conditioning (programming) mechanisms and their influence on infants’ cardiovascular health.A major strength of our study is the assessment at birth of surrogate markers of cardiovascular disease (CVD) (left ventricular mass index and subclinical atherosclerosis (carotid intima- media thickness)).Acknowledged limitations are the relatively small sample size, the potential for residual confounding and the limited representativeness of our sample (monocentric study).A better understanding of the clinical impact of the maternal hyperglycaemic disorders on offspring’s health early in life is needed to inform strategies for the early prevention of CVD.A long-term follow-up of children is planned for further assessment of their cardiovascular health.

Following the results of these studies, the International Association of Diabetes and Pregnancy Study Groups (IADPSG) have proposed new criteria to diagnose GDM.^3^ The benefits of screening and treatment of GDM have long been debated^14–17^ and recommendations from medical societies varied from no screening at all, screening only high-risk women (risk-based screening), to universal screening. Thus, the IADPSG recommend universal one-stage screening procedure that includes a 2-hour 75 g oral glucose tolerance test (OGTT). A single abnormal glucose concentration at fasting, at 1 hour or at 2 hours is sufficient for the diagnosis of GDM.^14^ New blood glucose threshold were derived from the HAPO study and based on pregnancy outcomes associated with the glucose level.^10 14^ Using these criteria, the prevalence of GDM is expected to be high, reaching up to 10%–20% of pregnant women in US populations.^3^

## Cardiometabolic effects of maternal DM

Maternal hyperglycaemic disorders are associated with fetal cardiac and vascular structural and functional alterations. For instance, it is well known that offspring of T1/T2DM mothers are at increased risk of congenital cardiac malformations and cardiac hypertrophy.^8 18^ In a retrospective study of 92 offspring of 87 diabetic mothers conducted in Lausanne, we observed that 5 neonates had congenital heart disease and 12 had ventricular hypertrophy.^8^ There is also growing evidence that maternal hyperglycaemic disorders may be involved in the ‘foetal programming’ of obesity and metabolic disorders in their offspring.^11 19^ Within a Developmental Origin of Health and Disease (DOHaD) framework,^20 21^ fetal programming (or conditioning) is the process involved in the associations between the exposure to detrimental factors during foetal life and health outcomes later in life.^22^ Foetal programming is suspected to be involved in the development of cardiometabolic disorders, such as elevated blood pressure, coronary heart diseases or DM, notably through epigenetic mechanisms.^20 21^ Despite recent and large growth in this research area, studies are needed to better objectively characterise both early life exposures and cardiometabolic outcomes.^23^

Intrauterine exposure to high maternal blood glucose is associated with foetal hyperinsulinism which is responsible for structural and functional changes affecting mostly the liver and the cardiovascular system. The liver is the major metabolic organ, considered as the metabolic brain and responsible for the distribution of the placental resources.^24^ Recent studies have shown that macrosomic offspring had impaired liver blood perfusion that contributes to foetal growth alteration^25–27^ and that differential perfusion of the foetal liver modified hepatic metabolic function and size.^24^ Studies indicate that the liver is enlarged in foetuses of T1/T2 DM mothers.^28 29^ Furthermore, and similarly the foetal heart response to hyperinsulinism is the development of an asymmetrical hypertrophy predominant at the septal wall. The evaluation of liver volume, interventricular septum thickness and left ventricular mass is therefore of outmost importance and may represent surrogate markers of the foetal metabolic response to maternal GDM.

## Lack of data on the effects of GDM on offspring’s cardiovascular health

Most studies on the effect of maternal hyperglycaemic disorders were conducted among mothers with T1/T2DM, not among mothers with GDM and with an emphasis on the effects on offspring’s metabolic outcomes rather than on offspring’s cardiovascular health. It is also unknown whether treatment of GDM is effective to reduce long-term risk of offspring’s metabolic and cardiovascular disease (CVD) risk^9 11 15^ and the new definition of GDM calls also for the conduction of further studies on the impact of GDM on offspring’s cardiovascular health. To study the early development of atherosclerosis and pathogenesis of CVD, it has become central to assess surrogate markers of CVD such as increased cardiac mass (left ventricular mass index; LVMI)^30^ and of subclinical atherosclerosis (assessed through carotid intima-media thickness; cIMT).^30 31^ These markers have been used extensively in studies in children and young adults with CVD risk factors.^30–34^ However, to our knowledge, the effects of GDM on offspring’s foetal and early neonatal cardiovascular health, and in particular on such surrogate markers,^31^ have never been studied.

## Objectives

Our objectives are to assess the effect of GDM on offspring’s cardiovascular health early in life, namely on (1) the surrogate markers of CVD and atherosclerosis at birth (LVMI and cIMT) (primary outcomes) and (2) the cardiovascular structure and function during the foetal period and potential neonatal cardiovascular risk factors (secondary outcomes).

## Methods and analysis

### Study design

We plan to conduct a cohort study of 200 offspring of women aged 18 years old or more. We will include 100 women with GDM and 100 without GDM. All pregnant women attending the antenatal care clinic or the GDM clinic at the Lausanne University Hospital (CHUV) will be invited to participate. In addition, women with GDM who are followed up by private diabetologists and gynaecologists in the Canton de Vaud will be invited to participate following a similar procedure. Using the new criteria of the IADPSG, the expected prevalence of GDM in this population is at least ~10%.^3^ Women with T1/T2D will not be included.

## Study population

Inclusion criteria: Pregnant women aged 18 years or older, with or without GDM at 24–32 weeks of gestation, and understanding French or English. Exclusion criteria: Women on strict bed rest, with pre-existing DM or severe mental disorders precluding participation.

## Study outcomes

Primary outcomes are surrogate markers of CVD and atherosclerosis at birth, that is, LVMI and cIMT. Secondary outcomes are foetal cardiovascular structure and function (notably LVMI and liver volume) and potential neonatal cardiovascular risk factors (including cord blood lipid levels, glycaemia, insulin, high-sensitiviy C reactive protein (hs-CRP), etc).

## Data collection and visits

During pregnancy, in the pre-recruitment phase, all pregnant women without pre-existing DM, attending the CHUV antenatal care clinic, have a fasting blood glucose measurement between the 24th and 28th weeks of gestation. GDM is diagnosed if fasting blood glucose is equal to or above 5.1 mmol/L. If fasting blood glucose is equal to or above 4.4 and below 5.1 mmol/L, pregnant women have a 2-hour 75 g OGTT and GDM will be diagnosed based on the new criteria of the IADPSG.^3 9^ Women screened by private obstetricians in the Canton de Vaud undergo either the same procedure or directly a 2-hour 75 g OGTT. Considering the variability in patients' compliance and time of enrolment for prenatal care, all eligible women, having been screened for GDM before 32 weeks of gestation, will be invited to participate (see inclusion and exclusion criteria in the Study population section).

The participation in the study is voluntary and involves a sequence of events and measurements as summarised in table 1.

**Table 1 T1:** Schedule of events and main assessments

	Visit	Period (WG)	Mother	Fetus/newborn
Pregnancy	V1 (Baseline)	24th to 32nd	Information notably on socioeconomic characteristics, general health, family history of CVD or diabetes and smoking and drinking habits Weight and height measurements Three blood pressure measurements Blood sampling	N/A
	V2	30th to 34th	Weight Three blood pressure measurements	Foetal cardiac echography
Delivery or postdelivery	V3	Birth	Blood sampling	Cord blood sampling, newborn weight, length and other birth-related information
	V4	2–7 days after birth	Weight Three blood pressure measurements	Neonatal cardiac echography and carotid echography

CVD, cardiovascular diseases; N/A, not applicable; WG, weeks of gestation.

At the first study visit (V1), scheduled between the 24th and 32nd weeks of gestation, a baseline assessment of the mothers will be conducted through means of self-report questionnaires and a researcher-administrated interview, weight, height and blood pressure measurements, and a maternal blood sampling. This will provide information notably on the socioeconomic status, general health status, family medical history of CVD or diabetes, smoking and drinking habits and several cardiometabolic biomarkers, all of which will be treated as potential confounding factors. If available, paternal data on the family history of CVD or diabetes will be also collected at the first study visit.

At the second visit (V2), between the 30th and 34th weeks of gestation, a foetal echography will be performed to assess the fetal cardiac structure (including LVMI) and function, the fetomaternal circulation, and the hepatic volume.

In women with GDM, information about treatment and blood glucose measurements will be recorded during the whole pregnancy.

At birth (V3), maternal characteristics (including mode of delivery, gravidity, parity, etc) and neonatal characteristics (including gestational age, sex, weight, length, etc) will be assessed. A sample of umbilical cord blood will be collected to measure various biomarkers, including glucose, insulin, total cholesterol, low-density lipoprotein (LDL)-cholesterol, high-density lipoprotein (HDL)-cholesterol, triglycerides, uric acid, creatinine, hs-CRP and various miRNA.

An echocardiography will be done to assess cardiac structure (including LVMI) and function 2–7 days after birth (V4). cIMT will be measured to assess vascular structure.

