## Measurements methods

### Maternal clinical assessment

Maternal body weight and blood pressure (three readings at 2-min intervals with a clinically validated^35^ oscillometric sphygmomanometer (OMRON HEM-907)^36 37^) will be measured during pregnancy (V1, V2) and in postpartum (V4). Clinical chemistry (including glucose, hemoglobinA1c (HbA1c), insulin, total cholesterol, LDL-cholesterol, HDL-cholesterol, triglycerides, uric acid and creatinine) will be assessed at the first study visit (V1) and blood will be collected for further potential analyses. All samples will be managed and stored in a biobank. The clinical data assessed as part of the usual care of the mother and potentially influencing the outcomes of interest will be collected. Also, information on socioeconomic characteristics, general health, family history of CVD or diabetes, smoking and drinking habits and so on will be gathered using a self-report questionnaire and a researcher-administrated interview.

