**Figure 1 F1:**
[figure not shown]
Hypothetical and highly simplified causal relationships between gestational diabetes mellitus (GDM) and cardiometabolic disorders. Two pathways can be hypothesised: (1) a direct effect of GDM on offspring’s cardiometabolic disorders; (2) an indirect effect through the mediator large for gestational age (LGA). It means that if LGA was prevented, part of the effect of GDM on cardiometabolic disorders would be prevented. Several confounding factors (such as maternal obesity, weight gain during pregnancy, smoking, socioeconomic status or family history of cardiometabolic diseases) have to be accounted.

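### V1 glucose, HbA1c and insulin are classed as potential confounders, although they measure the exposure or its direct consequence

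*Protocol article*

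**What the plan says.** All places are in the protocol article.

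- **Role of the V1 data** (Data collection and visits). After listing what V1 provides, the text ends with "drinking habits and several cardiometabolic biomarkers, all of which will be treated as potential confounding factors". No marker is excepted.
- **What is measured at V1** (Maternal clinical assessment). "Clinical chemistry (including glucose, hemoglobinA1c (HbA1c), insulin, total cholesterol, LDL-cholesterol, HDL-cholesterol, triglycerides, uric acid and creatinine) will be assessed at the first study visit (V1").
- **How the exposure is defined** (Data collection and visits). "GDM is diagnosed if fasting blood glucose is equal to or above 5.1 mmol/L"; women with fasting values from 4.4 to below 5.1 mmol/L go on to an OGTT. Some privately screened women go straight to the OGTT.
- **Order of events** (same section). In the pre-recruitment phase, women at the hospital clinic "have a fasting blood glucose measurement between the 24th and 28th weeks of gestation". Then "all eligible women, having been screened for GDM before 32 weeks of gestation, will be invited to participate". The baseline visit follows: "At the first study visit (V1), scheduled between the 24th and 32nd weeks of gestation".
- **Planned model** (Statistical analysis). Linear regression of each outcome on GDM yes/no. The list of confounders is open-ended: age, BMI, blood pressure, socioeconomic status, personal history of CVD and GDM treatment. It neither names nor excludes any biomarker.

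**The concern.** A confounder is a common cause of exposure and outcome, or a proxy for one. Here the exposure is a glucose measurement cut at a threshold. A further glucose reading or an HbA1c taken at or after that measurement is largely the same quantity on a continuous scale, and maternal insulin is closely tied to it.

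The section Cardiometabolic effects of maternal DM gives the mechanism under study: high maternal glucose leads to foetal hyperinsulinism, which alters the liver and heart. Holding maternal glycaemia fixed closes that route.

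The Objectives ask for the effect of GDM on LVMI and cIMT. With V1 glycaemia in the model, the GDM coefficient answers another question: whether the diagnosis matters between women with the same glycaemia. A null answer to that could be reported as no effect of GDM. Both primary outcomes are affected.

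**Working it through.** **1. Timing.** Screening precedes invitation and invitation precedes V1, so V1 blood is drawn at or after the measurement that defines GDM. Diagnosis and any treatment may already have changed the values by then.

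**2. The plan's own sample size.** Inputs from Sample size: LVMI 30 versus 32 g/m^2.7, SD 4.5, two-sided alpha 0.05, power 80%.

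- n per group = 2 × [4.5 × (1.960 + 0.842) / 2]² = 79.5, rounded up to 80. This agrees with the article.
- Standard error of the difference at 80 per group = 4.5 × √(2/80) = 0.712. Then 2/0.712 = 2.81 and power = Φ(2.81 − 1.96) = 0.80.

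The sample size is not in dispute. It is the reference point for what follows.

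**3. What adding a marker does.** Let R² be the share of variance in the GDM indicator explained by the marker, and d the GDM coefficient left after adjustment. The variance of the coefficient is multiplied by VIF = 1/(1 − R²), and

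power ≈ Φ(d × √(1 − R²)/0.712 − 1.96).

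The small opposite tail is included in the figures below. The residual SD is kept at 4.5.

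**4. Illustration A (assumed inputs).** Fasting glucose is Normal(4.5, SD 0.45) mmol/L, GDM is 5.1 or above, groups are sampled 1:1, and the whole effect of 2.0 runs through glucose. V1 glucose is the same value plus noise.

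| Noise SD | GDM coefficient after adjustment | VIF | Power from collinearity alone (d kept at 2.0) |
|---|---|---|---|
| 0.45 | 1.4 | 1.7 | 58% |
| 0.30 | 1.0 | 2.1 | 49% |
| 0.20 | 0.6 | 2.5 | 42% |

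**5. Illustration B (assumed inputs).** GDM is the top 10% of a screening measure with reliability 0.7, groups are sampled 1:1, and the whole effect of 2.0 runs through underlying glycaemia. The V1 marker is a separate noisy reading of that glycaemia.

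| Marker reliability | GDM coefficient after adjustment | R² | Power from collinearity alone | Power with shrinkage as well |
|---|---|---|---|---|
| 0.3 | 1.59 | 0.18 | 72% | 53% |
| 0.5 | 1.25 | 0.29 | 66% | 32% |
| 0.7 | 0.82 | 0.39 | 59% | 15% |
| 0.9 | 0.31 | 0.48 | 53% | 6% |

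**6. Sensitivity to OGTT diagnoses.** Illustration A defines GDM by fasting glucose only, but the article also diagnoses by OGTT. If 30% to 50% of cases are diagnosed by OGTT alone (assumed, with a fasting/OGTT correlation of 0.2 to 0.6), VIF is 1.3 to 1.9 and power from collinearity alone is 52% to 69%.

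**7. Combined range.** The coefficient falls from 2.0 to about 0.3 to 1.6. Collinearity alone takes power from 80% to roughly 42% to 72%.

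**The case against.** **The text says potential confounders, and no stated model contains these markers.** This is true. The sentence stands in a data-collection paragraph, the Statistical analysis section names no biomarker, and including glucose, HbA1c and insulin among the unnamed cardiometabolic biomarkers means joining two sections. A reader might infer that the plan has already fixed an adjustment for glucose; the document does not show that. What stands is that the sentence covers all the V1 information, excepts nothing, and is not overridden by an open-ended list.

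**The full analysis plan would settle the covariates.** The choice of covariates may well be left to it. But the article makes a positive statement about their role, which such a plan would have to contradict.

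**Measurement after diagnosis does not rule out confounding.** This is right, and it limits the point. A reader might infer that nothing measured at V1 can be a confounder. V1 lipids, uric acid, creatinine and blood pressure may partly reflect metabolic status before GDM, and the Introduction reports a large cohort study that corrected for maternal obesity and blood pressure. The Figure 1 legend names "Several confounding factors (such as maternal obesity, weight gain during pregnancy, smoking" and further factors, but it does not limit weight gain to the period after diagnosis and describes the diagram as highly simplified. None of these is shown to be an error.

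**The numbers are built on assumptions.** They are. Shrinkage follows from routing the whole effect through glycaemia, and the documents give no glucose distribution, marker reliability, OGTT share or mediated share. Treatment before V1 could weaken the collinearity or make the bias depart from simple shrinkage.

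**Mediation analyses are planned.** They concern LGA or birth weight and treatment, not maternal glycaemia.

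**Conclusion.** The concern holds for V1 glucose, HbA1c and insulin. If the stated rule were followed, the model would condition on the exposure or its immediate consequence and would no longer estimate the total effect of GDM on LVMI and cIMT. The expected result is generally a smaller coefficient, with a larger variance.

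The size is illustrative only: a true difference of 2.0 g/m^2.7 falling to about 0.3 to 1.6, and power of roughly 42% to 72% from collinearity alone. The actual loss depends on marker reliability, the share of the effect that runs through glycaemia, the share of GDM diagnosed by OGTT, and treatment before V1. Removal is partial unless the marker captures glycaemia almost completely, so the document does not support saying that the effect would vanish.

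The point does not establish that V1 lipids, uric acid, creatinine, blood pressure or weight gain must be left out.

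**What to change.** - **Data collection and visits:** amend the sentence so that V1 glucose, HbA1c and insulin are not among the potential confounding factors.
- **Statistical analysis:** state that these three markers do not enter the model for the total effect of GDM on LVMI and cIMT, and are used only in exposure-severity (dose-response) or mediation analyses.
- **Primary adjustment set:** base it on factors that plausibly precede GDM, such as maternal age, socioeconomic status, smoking, family history of diabetes or CVD, parity, and the earliest recorded BMI where available.
- **Optional:** a sensitivity analysis with and without V1 lipids, uric acid, creatinine, blood pressure and weight gain.

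The cost is wording. Most of the proposed factors are already collected at V1, and parity at birth. The article does not say that pre-pregnancy weight is recorded (V1 weight is taken at 24 to 32 weeks), so whether an earlier BMI can be obtained needs checking. Sample size and visits are unchanged, and leaving the markers out keeps the planned contrast at 80% power with 80 per group.

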## Measurements methods

### Maternal clinical assessment

Maternal body weight and blood pressure (three readings at 2-min intervals with a clinically validated^35^ oscillometric sphygmomanometer (OMRON HEM-907)^36 37^) will be measured during pregnancy (V1, V2) and in postpartum (V4). Clinical chemistry (including glucose, hemoglobinA1c (HbA1c), insulin, total cholesterol, LDL-cholesterol, HDL-cholesterol, triglycerides, uric acid and creatinine) will be assessed at the first study visit (V1) and blood will be collected for further potential analyses. All samples will be managed and stored in a biobank. The clinical data assessed as part of the usual care of the mother and potentially influencing the outcomes of interest will be collected. Also, information on socioeconomic characteristics, general health, family history of CVD or diabetes, smoking and drinking habits and so on will be gathered using a self-report questionnaire and a researcher-administrated interview.

